Glycocalyx regulates vascular permeability and inflammation and coagulation on the endothelial surface. Sphingosine-1-phosphate (S1P) in plasma regulates the synthesis and degradation of glycocalyx [21]. Furthermore, S1P modulates continuity of tight junctions, another factor related to vascular permeability. Serum albumin is essential for the bioavailability of S1P [22]. Albumin not only triggers the release of S1P from red blood cells, the main reservoir of S1P in blood, but also carries it to S1P-receptors on endothelial cells. Activation of S1P-receptor 1 on endothelial cells inhibits matrix metalloproteinase 9 and matrix metalloproteinase 13 dependent shedding of syndecan-1 ectodomain, an important component of glycocalyx [23]. Removal of plasma proteins from the culture media results in destruction of glycocalyx [23]. Conversely, in experimental heart transplantation, addition of albumin into the storage solution preserves glycocalyx of the coronary circulation [24]. If the CPB circuit is primed only with crystalloid solution, initiation of CPB will result in prompt and profound hypoalbuminemia.

No large RCTs comparing albumin solution to crystalloid solution in cardiac surgical patients have been conducted. Herein, we describe the final protocol (version 5, 3 September, 2018) for a randomized, parallel-group, double-blind study comparing 4% albumin solution to Ringer’s acetate solution in cardiac surgery with CPB. We hypothesize that CPB priming and intravascular volume replacement therapy using 4% albumin causes less major adverse events (MAE) than Ringer’s acetate solution.

The article is written in accordance with the Standard Protocol Items: Recommendations for Interventional Trials (SPIRIT) guidelines. The SPIRIT checklist is provided as Additional file 1.

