### Sample size analysis

In the literature, the incidence of MACE after cardiac surgery varies between 11 and 40%. The primary end-point in the present study, composite MAE, is broader than MACE and includes the latter. In a previous cohort study at the study site (Helsinki University Hospital, Meilahti hospital) the incidence of MAE was 30%. Thus, this incidence was used in the sample size analysis. Originally, it was estimated that 621 patients per group would be required to detect a 7.5%-unit absolute difference between the study groups in the primary outcome measure (proportion of patients with at least one MAE) with a two-sided significance level α = 0.05, and power of 80%. Accordingly, the original sample size was 1250 patients.

A predefined confirmatory analysis of incidence of MAE among the first 550 patients was performed for potential adaptation of the sample size in order to preserve the 80% power to detect a 7.5%-unit absolute difference between the study groups. The MAE incidence after 550 patients was 42%. In empirical analysis (without breaking the allocation code) the assumption of 50% and 42.5% MAE incidence in the two study groups turned out to be the “worst case scenario” (i.e., the highest needed patient number) with an estimate of 693 patients required for both patient groups. In accordance with the new power analysis, the sample size was increased by 2 × (693 − 1250/2) = 136 patients. Hence, the final adapted sample size will be 1250 + 136 = 1386. The Data and Safety Monitoring Board (DSMB) approved the extension of sample size and a decision was made before the interim analysis of 600 patients. Withdrawn patients or those who drop out, for whom the primary endpoint cannot be assessed, will be replaced.

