### Statistical analyses

The primary efficacy endpoint will be the proportion of patients with at least one MAE in the study groups during the study period of 90 days. Conclusions from this study will be based on analyses conducted under the principle of intention-to-treat. For primary outcome, The Lan-DeMets spending function with O’Brien-Fleming type boundaries will be employed to preserve the overall two-sided type I error rate at the 0.05 significance level. The main conclusions of the study on primary outcome will be based on Fisher’s exact test between the treatment groups. The exact boundary values are *p* = 0.00132 in the interim analysis and *p* = 0.04868 in the final analysis.

For the primary outcome variable and for MACE and AKI incidence of the secondary outcomes, a time-to-event analysis will also be performed. The timing of MAEs is classified into four categories: 1) in the operating theatre, 2) in the intensive care unit, 3) during the primary stay at the ward of Meilahti hospital, and 4) after the primary stay at Meilahti hospital during the 90-day follow-up period.

For secondary outcomes, the proportions are compared with Fisher’s exact text and logistic regression models. For continuous variables, *t*-test and linear regression models will be used to evaluate differences between the treatment groups. All the analyses regarding the secondary outcomes will be conducted with a two-sided significance level of 0.05. No correction for the significance level will be done due to multiple testing.

Subgroup analyses will be conducted by preoperative glomerular filtration rate (GFR), EuroScore, and operation type. For GFR and EuroScore, the patients will be divided into two groups: those with a value higher and those with a value lower than the median value. For operation type, the patients will be divided into those operated on for aortic valve stenosis (including patient with other surgical corrections in addition to aortic valve stenosis) and those patients without correction of aortic valve stenosis.

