The safety analysis is based on comparison of serious adverse events (SAE) between the study groups. Due to its nature, a MAE is always also a SAE. However, a MAE is not reported as a SAE in order to avoid double reporting. Consequently, the final number of SAEs is the sum of MAEs and the events reported as a SAE. Because a single patient may have more than one SAE, three different statistical analyses will be conducted for evaluation of study safety:
The number of patients with at least one SAE using Fisher’s exact testThe SAE number per a patient within those study patients with at least one SAE using *t*-testThe SAE number per a patient within all study patients using *t*-test

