### Interim analysis

One interim analysis will be conducted after 600 patients have been recruited and followed for 90 days. The principle of intention-to-treatment will be followed in all group comparisons of the interim analysis. The primary efficacy analysis (MAE) and safety analysis (MAE + SAE) will be conducted as described in the “Statistical analyses” section above.

The Data and Safety Monitoring Board will recommend pausing or stopping the trial if group difference in the primary outcome measure (proportion with at least one MAE) is found to be statistically significant at group sequential monitoring boundaries using Lan-DeMets spending functions. The exact boundary value for the interim analysis is *p* = 0.00132.

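### The second safety test compares SAE counts only among patients who had an SAE, so its p-value need not point to the safer arm; report it descriptively.

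*Protocol article*

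**What the plan says.** The safety paragraph under Statistical analyses in the protocol article sets three comparisons between the arms:

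1. Fisher's exact test on the number of patients with one or more SAEs.
2. A t-test on the "SAE number per a patient within those study patients with at least one SAE".
3. A t-test on the SAE count in all patients ("SAE number per a patient within all study patients using" the same test).

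The three are listed side by side. None is ranked above another, and the second is not marked as descriptive. Every MAE is also counted: "the final number of SAEs is the sum of MAEs and the events reported as a SAE". The Interim analysis section repeats the set at 600 patients: "The primary efficacy analysis (MAE) and safety analysis (MAE + SAE) will be conducted as described". The trial hypothesis in the Background is that treatment "using 4% albumin causes less major adverse events (MAE) than Ringer’s acetate solution".

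**The concern.** Having at least one SAE is itself the outcome of the first safety test. Restricting the second test to those patients conditions on something that happens after randomisation and that treatment may alter. Because MAEs count as SAEs, any effect on the primary endpoint also changes who enters the subset.

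Suppose albumin spares patients who would have had one SAE. They leave the albumin subset, the remaining patients have a higher average count, and the test moves towards harm although albumin has only prevented events. Suppose instead that albumin adds one SAE to patients who would have had none. They join the subset with a count of one, pull its average down, and the test moves towards benefit. The second error is the more serious one in a safety analysis.

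**Working it through.** **Inputs from the article.** Sample size analysis: 50% versus 42.5%, a 7.5-point difference, two-sided 0.05, 80% power, 693 per group. Interim analysis: 600 patients, so 300 per arm.

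**The article's own figure.** With pooled variance and mean proportion 0.4625:

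n = [1.96·√(2·0.4625·0.5375) + 0.8416·√(0.5·0.5 + 0.425·0.575)]² / 0.075² = 692.6, so 693 per group. This matches.

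**Assumptions.** The article gives neither an SAE count distribution nor a significance level for the safety tests. The distributions below are assumed, the level is taken as two-sided 0.05, and the t-test uses pooled variance. For illustration, the 7.5-point effect is applied to the proportion with any SAE.

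**One case by hand (distribution A).** Ringer: 50% of patients with no SAE, 30% with one, 20% with three. Albumin moves 7.5 points from one SAE to none.

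- Mean over all patients: Ringer 0.30·1 + 0.20·3 = 0.90; albumin 0.225·1 + 0.20·3 = 0.825. Albumin is better.
- Mean among affected patients: Ringer 0.90/0.50 = 1.80; albumin 0.825/0.425 = 1.94. Albumin looks worse by 0.141.
- Variance among affected patients, 4·p·(1−p) with p the share having three: Ringer 4·0.4·0.6 = 0.96; albumin 4·0.4706·0.5294 = 0.997.
- Expected affected patients: 693·0.50 = 346.5 and 693·0.425 = 294.5.
- Standard error: √(0.96/346.5 + 0.997/294.5) = 0.0785. Ratio: 0.141/0.0785 = 1.80.
- Chance of significance against albumin: P(Z > 1.96 − 1.80) = about 0.44. Simulation gives 43%.

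**The opposite case (A).** Albumin adds one SAE to 7.5% of patients. The all-patient mean rises from 0.90 to 0.375 + 0.60 = 0.975, but the mean among affected patients falls from 1.80 to 0.975/0.575 = 1.70. In simulation the second test significantly favours albumin in about 30% of trials.

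**Range over distributions and mechanisms** (simulated; 693 per arm and a 7.5-point fall in patients with any SAE unless stated). Distribution B is Ringer 50/25/15/10% with 0/1/2/3 SAEs.

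| Who is spared | Assumed Ringer distribution | Second test significant against albumin | In favour |
|---|---|---|---|
| Single-SAE patients only | A | 43% | at most 0.2% |
| Single-SAE patients only | B | 51% | 0.0% |
| Single-SAE patients only | 50/30/12/5/3% with 0 to 4 | 32% | 0.0% |
| Single-SAE patients only | 50/40/8/2% with 0 to 3 | 17% | 0.1% |
| Single-SAE patients only | 58/21/12.6/8.4% with 0 to 3 | 60% | 0.0% |
| Single-SAE patients only, 300 per arm | B | 25% | 0.1% |
| Low-risk patients only | Poisson mixture | 7.5% | 0.8% |
| Affected patients, whatever their count | A | 2.7% | 2.2% |
| Affected patients, whatever their count | B | 2.6% | 2.5% |
| Each event independently | A | 0.0% | 78% |
| Each event independently | B | 0.0% | 95% |
| Uniformly lower rate | Poisson | 0.0% | 41% |

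With A and single-SAE patients spared, effects of 5 and 10 points give 22% and 70% against albumin.

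**The all-patient tests on the same data.** Under B with single-SAE patients spared, the first test favours albumin in 79% of trials. The third favours it in 27% and points to harm in 0.1%.

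**The case against.** The strongest reply is that the valid comparisons are already in the plan. The first and third safety tests use all patients, and where the second test reverses they almost never agree with it. The only statistical stopping criterion in the Interim analysis section is the primary outcome at p = 0.00132, and no safety p-value is tied to a decision. Mortality and AKI are also separate secondary outcomes. All of this stands and limits the severity. It does not repair a test listed as the equal of the other two, because the article does not say which governs if they disagree.

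Three stronger readings are tempting and are not supported:

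- **That the test reverses under the very effect the trial hopes for.** The article states a difference in the proportion with a MAE. It does not say that only single-event patients benefit, and its rationale in the Discussion (less end-organ dysfunction, unimpaired coagulation) is broad. Under uniform prevention the test does not reverse.
- **That the test breaches intention-to-treat.** The article does say "The principle of intention-to-treatment will be followed in all group comparisons of the interim analysis", and also "Conclusions from this study will be based on analyses conducted under the principle of intention-to-treat". But no patient is moved out of the assigned arm, so a breach is arguable. The clear defect is selection on an outcome.
- **That counting MAEs as SAEs hides other harm.** This is a separate question, and nothing here measures it. The article defines the sum openly and also analyses MAEs alone.

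**Conclusion.** The concern holds for the second safety test only. As specified, it compares subsets that treatment can reshape, so a significant result in either direction cannot be read as evidence on safety.

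With 693 per arm and a 7.5-point effect, false harm occurs in about 17% to 60% of trials if only single-SAE patients are spared, and false benefit in about 30% (distribution A) if single SAEs are added. If patients are spared regardless of count, errors stay near nominal; if events are prevented independently, the direction is right. These figures rest on assumed SAE distributions and an assumed two-sided 0.05 level. Reversal is possible but not inevitable.

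The primary endpoint, the stopping rule and the first and third safety tests are unaffected. This is a should-fix point and does not threaten the trial's main conclusion.

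**What to change.** In the safety paragraph, and so wherever the Interim analysis section applies it, replace the second t-test with a table by arm of SAE counts among affected patients, labelled descriptive and without a p-value. State that safety inference rests on the two comparisons that use all randomised patients: the proportion with any SAE, and the SAE count per patient given as a mean difference or rate ratio with a confidence interval. If the interim report has already been made, apply the change to the final analysis.

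The cost is wording only. No further data are needed, and sample size, boundaries and conduct do not change.

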### Interim analysis

One interim analysis will be conducted after 600 patients have been recruited and followed for 90 days. The principle of intention-to-treatment will be followed in all group comparisons of the interim analysis. The primary efficacy analysis (MAE) and safety analysis (MAE + SAE) will be conducted as described in the “Statistical analyses” section above.

The Data and Safety Monitoring Board will recommend pausing or stopping the trial if group difference in the primary outcome measure (proportion with at least one MAE) is found to be statistically significant at group sequential monitoring boundaries using Lan-DeMets spending functions. The exact boundary value for the interim analysis is *p* = 0.00132.

### Unblinding

The trial will be double-blind. For safety reasons, however, a premature unblinding of a specific patient may take place in the following situations:
The investigator may request unblinding in case of an immediate safety hazard to the patient. Separate sealed envelopes for every allocation number will be available in this case.In case of a putative SUSAR, HUS Pharmacy, which will undertake randomization, will communicate directly with the Qualified Person Responsible for Pharmacovigilance of Sanquin Plasma Products B.V.

For interim analysis and after database lock at the end of the study, HUS-Pharmacy, which will generate the randomization and does not take part in patient care by any means, will separate the patients into two blinded treatment groups (marked by only “group 1” and “group 2”) for statistical analysis. The statistician who performs the analyses will be blinded for the treatment of these groups. The final unblinding will occur only after statistical analysis has been fully performed.

### Ethics approval, consent to participate, and ethical considerations

The operative ethics committee of Helsinki University Hospital approved the study protocol on 6 February 2017 (HUS/2917/2016). In addition, the Finnish Medicines Agency (Fimea, 136/ 2015) has approved the study protocol. Any modifications to the protocol will be immediately communicated to all responsible authorities. The trial will be performed according to the current version of the Helsinki Declaration (2013).

Eligible patients who undergo cardiac surgery at Meilahti Hospital (Helsinki University Hospital, Helsinki, Finland) will be recruited to the study. After obtaining informed consent, elective patients will be recruited during the perioperative screening visit for anesthesia. The patients scheduled for surgery during the index admission will be recruited as soon as the decision to perform surgery has been made and informed consent has been obtained.

Ringer acetate is used as conventional fluid therapy at the study site. In addition, albumin solutions are used after clinical consideration perioperatively. In a scientific literature review during the study design in 2013, a total of 25 RCTs with 1141 patients were found (Additional file 3). In priming fluid the maximum albumin dose was 80 g and the highest albumin concentration was 4%. The highest albumin dose for volume resuscitation was 254 g. The highest total albumin dose (including priming and volume resuscitation) was 267 g. No adverse events or transmitted infections were reported. In the present trial, the albumin dose in the priming fluid will be 60 g and the concentration 4%. The highest possible albumin dose for volume resuscitation will be 128 g, and thus the highest total albumin dose will be 188 g. According to the existing literature, the albumin doses administered in the present study are considered safe.

## Discussion

Optimal fluid therapy in adult cardiac surgery is not known. Patients receive large amounts of fluids during surgery, even though avoiding fluid overload and fluid extravasation may reduce complications [1–3]. Colloid use in cardiac surgery is preferred, but the data on the safety of HES solutions remain uncertain [10, 11, 26]. Thus, the assessment of the safety and efficacy of albumin solution in cardiac surgery is warranted.

The SAFE study is the only double-blind large scale trial on albumin use in fluid resuscitation thus far [27]. It compared the effect of albumin to saline on 28-day mortality in intensive care patients [27]. In terms of the clinical setting, there will be an essential difference between the SAFE study and the present study. In critically ill patients of the SAFE study, systemic inflammatory response and endothelial glycogalyx destruction had already begun before fluid resuscitation was initiated. This may have led to extravasation of the study fluid irrespective of its composition. In cardiac surgery glycogalyx is intact before CPB is initiated. Albumin in CPB priming prevents CPB-induced hypoalbuminemia and may reduce endothelial glycogalyx destruction and, thus, it may maintain microcirculatory function better [23, 24].

The theoretical basis of the present study is two-fold. First, by using albumin from the beginning of surgery and in CPB priming, i.e., before the onset of CPB, we hypothesize that albumin protects endothelial glycogalyx from destruction, preserves the microcirculation, and thus reduces end-organ dysfunction. Albumin may protect the glycocalyx also by reducing hypervolemia [19]. Second, albumin does not impair blood coagulation [15]. The primary outcome measure of the present study will be the composite end-point of MAEs, i.e., death, acute myocardial injury, acute heart failure, resternotomy, stroke, major arrhythmia, major bleeding, marked infection, or acute kidney injury. The primary outcome measure reflects both end-organ dysfunction and bleeding diathesis.

The present study will explore the effect and the safety of the 4% albumin in cardiac surgery with CPB compared to Ringer’s acetate. This study is the first large scale randomized, controlled, double-blind trial comparing albumin to crystalloid in cardiac surgery. No other such trial was registered in ClinicalTrials.gov as of July 31, 2019.

### Trial status

The first patient was enrolled on 21 March 2017 and the study is ongoing. At the time of submission the ALBICS trial has enrolled 1143 patients. The patient recruitment is expected to be completed in February 2020 and the follow-up in May 2020. The final protocol version is version 5, 3 September, 2018.

## Data Availability

According to the prevailing confidentiality regulations even pseudonymized data cannot be placed on a public domain. Only the designated trial investigators will have access to the personal data of participants and to the final data set.

## Abbreviations

AKI: Acute kidney injury
cGMP: Current Good Manufacturing Practise
CK-MB: Creatinine kinase muscle/brain isoenzymes
CPB: Cardiopulmonary bypass
CRF: Case report form
ECMO: Extracorporeal membrane oxygenation
EDTA: Ethylenediaminetetraacetic acid
EF: Ejection fraction
EVA: Ethyl vinyl acetate
GFR: Glomerul filtration rate
HES: Hydroxyethyl starch
ICH-GCP: International Council for Harmonisation Good Clinical Practice
ICU: Intensive care unit
MACE: Major adverse cardiac event
MAE: Major adverse effect
MAP: Mean arterial pressure
PRBC: Packed red blood cell
RCT: Randomized clinical trial
S1P: Sphigosine-1-phosphate
SAE: Serious adverse event
SPIRIT: Standard Protocol Items: Recommendations for Interventional Trials
SUSAR: Suspected unexpected serious adverse reaction
